#### Fecal samples.

Gut microbiota and other gut-related biomarkers will be measured using two types of fecal samples from the patients with AN and HC participants: (1) Fecal sample collected in DNA-preserving buffer (hereby referred to as ‘buffer fecal samples’) and (2) fecal samples collected in a container with an anaerobic pad (hereby referred to as ‘anaerobic fecal samples’). While buffer fecal samples will be used for biobanking and analyses such as DNA sequencing, anaerobic fecal samples will be used for in vitro fermentation experiments in WP2 and FMT mouse experiments in WP3. All patients with AN (at TP1–3) and HCs (at TP1 only) will collect two buffer fecal samples at each timepoint. Additionally, a subgroup of patients with AN from Oslo University Hospital and a subgroup of HCs will collect anaerobic fecal samples (at TP1 and TP3 for patients with AN, at TP1only for HCs). All participants will receive a fecal sample collection kit, along with a demonstration of its contents and oral instructions on proper collection procedures.

Buffer fecal samples will be collected using a Protocult Stool Collection Device (Therapak, Supplier No. 505000G) and Stool collection Tube with DNA stabilizer (INVITEK, Item No. 1038111200). Patients with AN will primarily collect buffered fecal samples upon enrollment at the clinics, preferably within one week of hospital admission (TP1), and again at the hospital at TP2 and TP3. HCs will collect fecal samples at home and send them by post to NMBU. At NMBU, the samples will be stored at −80°C for biobanking and until further processing.

Anaerobic fecal samples will be collected at the hospital unit (the Regional Department of Eating Disorders at Oslo University Hospital) for patients with AN and at home for HCs. All participants will be instructed to take a plum-sized fecal sample and place it in a container with an airtight lid. An anaerobic pad (AnaeroGen 2.5 L, Thermo Scientific) will be placed in the container to maintain anaerobic conditions. The container will then be stored in a refrigerator or cooling bag until further processing at NMBU. For the patients with AN, nurses and hospital personnel will assist with the procedure, while HCs will perform the procedure at home and temporarily store the sample in cooling bags until transportation to NMBU. Further processing of the anaerobic fecal samples will be conducted by trained students within 24 hours of sampling, following a standardized protocol at the NMBU laboratory.

The container with the anaerobic fecal sample will be opened in an anaerobic chamber (Whitley A85 Workstation; 85% N_2_, 5% CO_2_, 10% H_2_) or home-made anaerobic box (dry ice at the bottom and continuous flushing with CO_2_ and N_2_), and two 4-gram portions of fecal material will be weighed out. For WP3, 4 g fecal material will be dissolved in 40 mL freshly made reduced PBS (i.e., 45 mL anaerobic Dulbecco’s phosphate buffered saline (Sigma-Aldrich, #D8537), mixed with 45 mg L-cysteine hydrochloride (Sigma-Aldrich, #C1276), and 5 mL glycerol (Sigma-Aldrich, #G5516)), whereas the 4 g samples destined for WP2 will be dissolved in an anaerobic cryoprotective solution (0.1 M phosphate buffer pH 6.8, 15% (v/v) glycerol, 5% (w/v) sucrose, 0.1% (w/v) L-cysteine hydrochloride, 0.03% (w/v) riboflavin). Both suspensions will be homogenized at room temperature for five minutes at 30 Hz using Mixer Mill (MM 400, RETSCH). Next, the homogenates will be filtered (100 μm pore size), aliquoted (20 aliquots á 1.5 mL for WP2, 30 aliquots á 1 mL for WP3), snap frozen in liquid nitrogen, and stored at −80°C until use in the fermentation (WP2) and animal (WP3) experiments. If there is residual material, an aliquot of at least 0.6 g from the anaerobic fecal sample will be collected for SCFA analysis. Any excess fecal material from the anaerobic fecal sample beyond this will be stored in the NMBU biobank at −80°C. The protocol for the collection and processing of the anaerobic fecal samples was developed based on Bokoliya et al. [64] with the goal to ensure that the microbes in the samples will not be exposed to significant amounts of oxygen during processing.

#### Anthropometric measurements and medical records.

For the patients with AN, anthropometric measurements (body height and weight, and body weight history) will be gathered from medical records at each hospital. Results from blood serum analyses and information about medications, including the use of laxatives and dietary supplements, will also be recorded from the patient’s medical records. HCs will report their body weight and height as part of the self-report questionnaires but will be offered the opportunity to have new measurements taken at the hospital if necessary. Anthropometric measurements should be taken within a week of each time point.

#### National health registries.

The NORMA study has the approval to collect information about the participants’ through the Norwegian Prescription Database, the Norspis registry (Norwegian Quality Register for the Treatment of Eating Disorders), the Norwegian Patient Register, and the Norwegian Registry for Primary Health Care – used to record contacts with health services related to mental health treatment) at TP1–3 and after 1, 5 and 10 years after enrollment in the study. These data can provide detailed insights into antibiotic use and other relevant medication use for both the HC group and AN group, pertinent to the NORMA study.

#### Compliance strategies.

Patients with AN will receive a gift card worth 200 NOK for each completed time point. They will be informed about the gift cards at the time of recruitment and will be made aware that participation will involve additional follow-up and contact with study personnel during the study period. After participating in the study, the HCs will receive a personalized health report including information about their blood tests and nutritional status. Additionally, five gift cards worth 1000 NOK each will be given to randomly selected HCs at the end of the study.

#### Sample size calculations.

The sample size needed to detect statistically significant differences in the fecal microbiota composition between patients with AN and HCs at TP1 was estimated using a web-interface for simulation-based power calculations. A Dirichlet-Multinomial model is used to describe and generate abundances (fedematt.shinyapps.io/shinyMB) using the default setting except # of operational taxonomic units (OTUs) was set to 100, significance level (α) was set to 0.05, and the abundance curves were made based on the five most abundant OTUs increased by 60% and the five next most abundant OTUs increased by 50%. With these settings, the sample size required to detect a statistically significant difference between the patients with AN and HCs with 80% power will be 79 participants in each group. With an estimated drop-out of ~10%, we plan to include 90 patients with AN and 90 HCs.

#### Hypotheses and planned statistical data analyses in WP1.

The clinical observational trial in WP1 is designed to test the following hypotheses.

WP1, Hypothesis 1: The gut microbiota in patients with AN is different from that of HCs. We will compare different indices of alpha diversity, investigating both microbial richness and evenness, and different measures of beta diversity. Also, differences in bacterial abundances at various taxonomic levels (e.g., phylum, class, order, family, and genus) will be investigated using conventional statistical approaches as well as more advanced multivariate methods.WP1, Hypothesis 2: Inpatient treatment of patients with AN combining cognitive treatment with re-nutrition strategies will change the gut microbiota in a more normalized direction (more similar to HCs). Mixed models will be applied to statistically analyze the effect of time on different indices of alpha diversity and bacterial abundances at various taxonomic levels (e.g., phylum, class, order, family, and genus) with and without adjusting for baseline characteristics such as age and BMI. Differences in the overall bacterial communities between the patients with AN at the different visits and HCs based on the beta diversity measures will be assessed using methods such as global permutation based multivariate analysis of variance (PERMANOVA).WP1, Hypothesis 3: Gut microbiota composition in patients with AN at TP1 (before treatment) is associated with serum biomarkers such as biomarkers of appetite regulation and inflammation, dietary characteristics, GI issues, and mental issues, and can be used to predict treatment success in terms of improved BMI and EDE-Q-scores. Associations between relevant parameters will be analyzed using multivariate analysis such as principal components analysis (PCA), canonical variate analysis, independent components analysis, and multivariate regression. Regression models will be used to investigate associations between microbial diversity and clinical outcomes, adjusting for age and BMI. Machine learning approaches such as partial least squares regression, gradient boosting, or artificial neural network algorithms will be used to predict the response variables (clinical outcomes and treatment success), from the large set of predictor variables; microbial taxa, gene, or pathway content.WP1, Hypothesis 4: Changes in microbiota composition during inpatient treatment towards that of HCs are associated with improvements in BMI as well as improvements in dysregulated serum biomarkers, GI complaints, and mental health. Associations will be analyzed using similar strategies as described in hypothesis 3.

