The human microbiota refers to the vast collection of microorganisms that colonize the human body, whose genomes encode more than three million genes that play a significant role in both physical and mental health [20]. The majority of these microbes reside in the GI tract and include bacteria, viruses, fungi, and other microbes [20]. Although the gut microbiota has a heritable component and is affected by age, its composition is mainly influenced by environmental factors, with diet being the most potent modulator [20,21]. Patients with AN often display abnormal dietary patterns, including low energy intake, limited food variety, and fat avoidance [22,23], and patients undergo substantial nutritional changes during treatment. Indeed, substantial evidence reveals that the gut microbiota in individuals with AN is different from healthy controls (HCs), affecting both microbial composition and function [18,24–27]. These differences are often referred to as gut microbiota dysbiosis or imbalance [2,19].

The gut microbiota in individuals with AN has been found to differ from that of HCs in several ways. Multiple studies have reported reduced bacterial richness and evenness in AN, referred to as alpha diversity [19,27–29], with one study showing correlation between reduced bacterial richness and depression as well as core ED psychopathology [28]. However, other studies have found no significant differences in diversity indices between AN and HCs [24–26,30], and findings related to beta diversity are similarly inconclusive [19]. Thus, while there is broad evidence of and compositional alterations (i.e., gut microbiota dysbiosis) in patients with AN compared to HCs [18,24–27], Scala et al. [19] highlight the lack of consensus concerning diversity and psychopathological symptoms in AN.

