#### Outcomes.

Primary outcomes for WP1 are: i) differences in fecal microbiota composition between AN and HCs, and ii) changes in fecal microbiota composition-, iii) changes in mental scores-, and iv) changes in GI problems, in AN during standards care treatment at the hospital units for ED.

Secondary outcomes for WP1 are: i) associations between microbiota measures and abundance of specific taxa, serum biomarkers, dietary characteristics, GI issues and mental issues, and ii) associations between baseline microbiota composition and changes in GI complaints during standard care treatment at the clinics for ED, and iii) associations between baseline microbiota composition and changes in mental scores during the standard care treatment at the hospital units for ED.

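### Hypothesis 1, the only WP1 question with a sample-size calculation, is to be answered by several unranked diversity measures and taxon comparisons, so neither the 5% level nor the 80% power belongs to an identified test

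*Protocol article*

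**What the plan says.** The Outcomes section of the protocol article lists four primary outcomes for WP1. The first is "differences in fecal microbiota composition between AN and HCs", with no metric attached.

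The section on hypotheses and planned analyses in WP1 turns this into one global statement, Hypothesis 1: "The gut microbiota in patients with AN is different from that of HCs". For its analysis it says "We will compare different indices of alpha diversity, investigating both microbial richness and evenness, and different measures of beta diversity". It adds bacterial abundances at several taxonomic levels, with phylum to genus as examples, which "will be investigated using conventional statistical approaches as well as more advanced multivariate methods". The number of indices, the dissimilarities and the tests are left open, and nothing is ranked.

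PERMANOVA is mentioned once, under Hypothesis 2. It is offered as an example of a method for comparing overall communities between AN visits and controls, on beta-diversity measures in the plural.

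The Sample size calculations section covers only the AN versus control comparison at TP1. There "significance level (α) was set to 0.05", power is 80%, and the result is 79 per group, raised to 90 for drop-out. The section does not say which test this alpha and power belong to, or whether the test is one- or two-sided.

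**The concern.** One yes-or-no claim is to be answered by a list of measures that can disagree, and the article gives no rule for what happens when they do. Disagreement is likely. The Background reports reduced alpha diversity in several studies, yet "other studies have found no significant differences in diversity indices between AN and HCs". It calls beta-diversity findings similarly inconclusive, while describing broad evidence for compositional changes. A reader of the final report could not tell whether the highlighted measure was chosen before or after the results were seen.

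Two properties are at stake. If a positive result on any measure is taken as support, 5% is not the error rate of the primary conclusion. And the 80% power cannot be checked, because the test it describes is not identified. The Discussion calls the trial well powered, and that description has the same gap.

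**Working it through.** **Inputs.** Alpha 0.05, 80% power, 79 per group, about 10% drop-out and 100 OTUs (ten of them raised by 60% or 50%) come from Sample size calculations. At least two alpha indices (richness, evenness) and at least two beta measures come from Hypothesis 1. Assumptions, not in the article: two-sided tests, exactly four global tests, and any significant result counted as support.

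**The plan's own figure.** The drop-out step is consistent: 79 / 0.9 = 87.8, so 88, against a planned 90. The 79 itself cannot be reproduced, because it rests on tool defaults and a test statistic that the article does not give. Dirichlet-Multinomial simulations at 79 per group used OTU-wise Wilcoxon tests, assumed 10,000 reads, overdispersion 0.01 to 0.10 and two assumed abundance curves. Average power for the ten changed OTUs with Benjamini-Hochberg adjustment ran from about 20% to over 99%. In the least favourable setting that average was 20.5%, while the chance of at least one Bonferroni-significant OTU was 78.7%. The same data thus give very different power according to which result counts. The 79 is neither confirmed nor refuted.

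**False-positive rate, four global tests.** For equicorrelated normal statistics with correlation ρ and c = 1.96:

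rate = 1 − ∫ φ(z) · [Φ((c − √ρ·z)/√(1−ρ)) − Φ((−c − √ρ·z)/√(1−ρ))]⁴ dz

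| ρ | Chance of at least one false positive |
|---|---|
| 0 | 1 − 0.95⁴ = 0.185 |
| 0.3 | 0.174 |
| 0.5 | 0.156 |
| 0.8 | 0.114 |

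**Check with correlated microbiome data.** A null Dirichlet-Multinomial simulation (79 per group, 600 replicates, 10,000 reads) kept the dependence between measures:

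| What counts as support | Overdispersion 0.05 | Overdispersion 0.01 |
|---|---|---|
| One pre-named PERMANOVA | 5.0% | 7.2% |
| Richness or evenness | 8.7% | 9.7% |
| Those two plus one beta measure | 13.2% | 16.5% |
| Two alpha and two beta measures | 17.5% | 21.0% |
| Two alpha, two beta, and taxa with Benjamini-Hochberg within each of five levels | 26.5% | 32.2% |

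Monte Carlo standard error is √(0.05 × 0.95/600) = 0.9 points for the first row and √(0.21 × 0.79/600) = 1.7 points at 21%. The permutation test holds its level under this null, so the 7.2% is sampling noise, and the 21.0% from the same replicates is probably a little high too. Independence gives 18.5%.

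The last row shows that false-discovery control within each taxonomic level would not settle the matter, because it leaves the choice between measures open.

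**The case against.** The strongest objection is that this is a condensed article and that an SAP, if one exists, is not shown. Choice of dissimilarity, order of testing and false-discovery settings commonly sit there. For taxon-level adjustment that stands, and its absence is not held against the plan. What remains is in the article itself: it sets several measures against one primary claim, attaches a sample size to that claim, and ranks none of them.

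Second, a reader might infer that the plan declares Hypothesis 1 confirmed on any one positive result. The article gives no decision rule, so that reading is an assumption, and the percentages above are conditional on it. A reader might also infer that taxa will be tested without correction, which would make a false positive close to certain. The article does not say so. The 100 OTUs are a setting of the power simulator, and Hypothesis 1 names phylum to genus as its example levels.

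Third, PERMANOVA is present, and the visits it covers could include TP1. That is fair. It is still only an example, on unnamed measures, under a different hypothesis.

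Fourth, the rates assume no true difference at all, whereas the Background cites substantial evidence of one, and the Discussion describes the aim as exploratory. Reporting several measures is a reasonable response to a conflicting literature. This tempers the practical risk of a wholly false conclusion. It does not settle which result answers a primary, powered question.

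**Conclusion.** The point holds in a limited form. The article names no deciding test for Hypothesis 1. If any significant result is read as support and nothing is adjusted across measures, four global tests at two-sided 0.05 give a false-positive rate of about 11% (correlation 0.8) to 21% (upper simulated value), roughly two to four times the nominal level. Those two conditions, the count of four and the simulation settings are assumptions. The 80% power and 79 per group are not shown to be wrong; they are not tied to an identified test. A reader might take 79 per group to be right for PERMANOVA on one dissimilarity, but the calculation is framed in OTU abundance shifts and does not support that without a further check. The data remain usable whatever is decided, so this should be corrected but does not threaten the study.

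**What to change.** In the Hypothesis 1 paragraph, name one deciding test for AN versus controls at TP1, at two-sided 0.05. One example is a single PERMANOVA on one named dissimilarity at one named taxonomic level. Make the other beta measures sensitivity analyses. Make alpha indices and taxon comparisons supportive, with false-discovery control for the taxa.

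In Sample size calculations, state which test the 79 per group and 80% power describe. If the deciding test differs, restate the power for it.

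Date the change before any AN-HC results are viewed. Data collection is expected to end on 31 May 2026 and first results in the second quarter of 2026, so time is short. If a dated SAP already names the test, a reference to it and the sample-size clarification would be enough.

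The cost is about a paragraph and possibly one power simulation, with no extra participants or samples. All planned analyses can stay. The downside is that a single index or taxon at nominal p<0.05 can no longer be called confirmation of Hypothesis 1.

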## Background

Anorexia nervosa (AN) is a severe eating disorder (ED) associated with high rates of medical complications, psychiatric comorbidities, and mortality [1,2]. The lifetime prevalence of AN in Europe is estimated to be 1–4% [3]. Globally, the AN prevalence is rising, especially among adolescents, and the COVID-19 pandemic may have further increased both the prevalence and severity of the condition [4]. In Norway, approximately 3000 females may require treatment for AN at any given time [5], and the incidence of AN in specialized health care services has increased post pandemic [6]. The etiology of AN remains elusive, yet it is clear that a combination of genetic [7] and environmental factors [8] significantly contributes to its development, with several risk factors identified [9]. Patients with AN often struggle with intense fear of weight gain, low weight, and ambivalence toward recovery, challenges that are compounded by significant gastrointestinal (GI) symptoms [10,11], reported in up to 90% of patients [12]. These factors may complicate treatment, leading to high dropout-rates [13], and present challenges not only to the patients, but also their families, clinicians and society at large, due to the high societal costs involved [14].

Currently, no gold-standard treatment exists for patients with AN. However, specialized care typically combines psychotherapy, nutritional therapy, and management of co-occurring complications and comorbidities. Unfortunately, treatment outcomes are often unsatisfactory [15], with approximately 50% of patients experiencing poor recovery and 20% developing a protracted course [16]. Despite its severity, current dietary interventions are largely based on clinical experience and general guidelines, rather than evidence-based treatments [17], underscoring the need for more effective treatment alternatives. In recent decades, there has been increased focus on the role of gut microbiota in AN, both in its potential involvement in pathogenesis [18] and as a promising therapeutic target [19].

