Due to the contradictory findings on bacterial alpha- and beta diversity measures, recent research on gut microbiota in individuals with AN has shifted the focus toward the investigation of specific microbial taxa [19]. For instance, reduced abundances of the bacterial genera *Roseburia*, *Lactobacillus*, *Faecalibacterium*, *Clostridium*, and *Bifidobacterium* have been associated with anxiety, depression, and AN-related psychopathology [19]. High abundance of the archaeon *Methanobrevibacter smithii* has also been observed in AN [24,30,31], a specie thought to contribute to constipation, a common GI symptom in this population [11]. Additionally, higher abundances of the genus *Sutterella* have been linked to greater weight gain at one year-follow up after treatment, suggesting its potential as a prognostic marker and therapeutic target [26]. Several studies have further associated gut microbiota dysbiosis with AN disease severity [18,28,29], possibly reflecting a metabolically dysfunctional microbial profile [32]. Nevertheless, the specific features of microbial alterations in AN remain unclear due to limited sample sizes, methodological differences, and contradictory findings across studies [19,33].

Particularly, the extent to which gut microbiota dysbiosis in AN normalizes or persists following weight restoration remains understudied, primarily due to the limited number of longitudinal studies that follow the patients throughout their treatment programs [19,33]. Moreover, the existing longitudinal studies often involve short follow-up periods, and many patients remain underweight at the conclusion of these studies, making it difficult to distinguish microbiota changes associated with underweight from those specific to AN. To date, Andreani et al. [26] have conducted the only study with a one-year follow-up, revealing persistent alterations in the gut microbiota composition throughout treatment. Furthermore, even one year after treatment and following weight restoration, the microbiota profile remained partially distinct from that of HCs. These findings align with other longitudinal studies with shorter follow-up durations, which also indicate a partial shift toward normalization during treatment, yet continued divergence from HCs persists [11,24–26,32,34].

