#### Overview of study design and procedures.

The schedule of assessments in WP1 is presented in **Fig 1**. The included patients with AN will be assessed throughout their participation in standard clinical treatment at three time points (TP): before the start of treatment and/or within the first week of admission (TP1, baseline), and at 6- and 12-week follow-up (TP2 and TP3, respectively). Patients will be asked to provide fecal samples, fasting blood samples, and complete questionnaires about their mental and physical health, as well as record their diet at each time point. The HC participants will be assessed at one time point only (referred to as ‘TP1’). The HCs will complete approximately the same digital questionnaires as the patients, provide blood and fecal samples, and record their diet for three days. The NORMA study has approval to contact the participant within ten years after recruitment for follow-up data collection and access to medical records and registry data.

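### Hypothesis 2 judges similarity to HCs from whichever AN samples exist at each visit, so a change in who is sampled can look like, or hide, normalisation

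*Protocol article*

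**What the plan says.** Hypothesis 2 (Protocol article, Hypotheses and planned statistical data analyses in WP1) expects inpatient treatment to move the AN microbiota towards that of HCs. Two analyses are given.

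- Within AN: "Mixed models will be applied to statistically analyze the effect of time on different indices of alpha diversity and bacterial abundances" at several taxonomic levels, with and without adjustment for baseline characteristics. HCs do not enter.
- Against HCs: "Differences in the overall bacterial communities between the patients with AN at the different visits and HCs based on the beta diversity measures", assessed by methods such as PERMANOVA.

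Other parts of the article bear on the second analysis:

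- Overview of study design and procedures: "The HC participants will be assessed at one time point only". One HC sample is therefore the reference for all three AN visits.
- Sample size calculations: "With an estimated drop-out of ~10%, we plan to include 90 patients with AN and 90 HCs".
- Background: complicating factors in AN treatment are described as "leading to high dropout-rates", and "Several studies have further associated gut microbiota dysbiosis with AN disease severity".
- Study participants: a stay of 12 weeks is presumed, not assured.
- Fecal samples: TP2 and TP3 stool is collected at the hospital.

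**The concern.** The HC reference is fixed, so any difference between the TP1, TP2 and TP3 contrasts comes from the AN side. It has two possible sources: patients changed, or different patients were sampled. A mixed model carries forward the TP1 information of a patient who later leaves. PERMANOVA does not, whether it is run once per visit or as one model over all visits: each visit's group location is that of the samples present.

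The mixed models in the same paragraph do not fill the gap. They cover alpha diversity and taxon abundances and do not measure distance to HCs. At community level, the claim that patients became more like HCs therefore rests on a contrast that cannot separate the two sources. A smaller gap at TP3, or a TP3 test that is no longer significant with fewer patients, could be reported as normalisation without any patient having moved. The opposite error is also possible.

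**Working it through.** **The plan's own figure.** 79 per group with 10% loss gives 79/(1 − 0.10) = 87.8, so 88. The planned 90 is close and allows for 1 − 79/90 = 12.2% loss. The 79 depends on web-tool defaults that are not printed, so it was not rerun.

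**Inputs.** From the article: 90 patients, about 10% loss, alpha 0.05, 80% power. Assumed: 20% and 30% loss, leavers 0.5-1 SD further from HCs at TP1, test-retest correlation 0.6, two-sided testing.

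**Step 1: false shift with no true change.** Shift = loss fraction × (leaver mean − stayer mean), in TP1 SD.

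**Step 2: paired detectable change.** With 81, 72 and 63 patients, it is 0.315, 0.335 and 0.359 SD *of the change score*. In TP1 SD, multiply by √(2(1 − 0.6)) = 0.894.

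| Loss | Patients left | False shift (TP1 SD) | Detectable change (TP1 SD) |
|---|---|---|---|
| 10% | 81 | 0.05-0.10 | 0.28 |
| 20% | 72 | 0.10-0.20 | 0.30 |
| 30% | 63 | 0.15-0.30 | 0.32 |

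A simulation (4,000 runs, n=90) gave 0.048/0.100, 0.101/0.202 and 0.146/0.297 for a leaver difference of 0.5/1 SD. The same-patient change was 0.00 under this mechanism, in which the leaver difference is persistent.

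**Step 3: scale against the AN-HC gap.** On one standardised measure, 79 per group detect 2.80 × √(2/79) = 0.446 SD. The false shift at 10% loss is then 0.05/0.446 = 11% to 0.10/0.446 = 22% of a just-detectable gap. If exactly the most dysbiotic 10% left, the shift would be 0.195 SD (44%). That is an extreme case.

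**Step 4: PERMANOVA itself.** Dirichlet-multinomial data were simulated with 100 OTUs and the article's +60%/+50% shift, using Bray-Curtis distance, an assumed concentration of 10 and 60 replicates per setting. The patients kept retain their TP1 samples, so nobody changes. Share of tests with p<0.05:

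| Loss | Selection correlation | All 90 | Random loss | Selective loss |
|---|---|---|---|---|
| 10% | 1 | 0.95 | 0.90 | 0.65 |
| 10% | 0.5 | 0.93 | 0.93 | 0.85 |
| 30% | 1 | 0.95 | 0.90 | 0.27 |
| 30% | 0.5 | 0.90 | 0.78 | 0.43 |

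Most of the fall comes from selection rather than from the smaller n. Sixty replicates make these shares approximate.

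**Step 5: which alternative is unbiased.** Fresh measurements were drawn at each visit (assumed intraclass correlation 0.7, 150 replicates), with loss depending on the observed TP1 value and no true change.

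| Loss | Selection correlation | Fall in by-visit gap | Mixed-model TP3 effect (SD) | Completers' paired change (SD) |
|---|---|---|---|---|
| 10% | 1 | 29% | +0.002 | +0.060 |
| 10% | 0.5 | 16% | +0.003 | +0.031 |
| 30% | 1 | 78% | −0.001 | +0.145 |
| 30% | 0.5 | 41% | −0.009 | +0.066 |

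The mixed model on all visits stays near zero. The completers-only change drifts away from HCs through regression to the mean, so it should not be the sole basis either.

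**The case against.** **The direction is not established.** A reader might infer that more dysbiotic patients will leave, so that the AN group will falsely look normalised. The documents do not support that. The Background links dysbiosis to severity, and dropout to fear of weight gain, ambivalence and GI symptoms; it never links dropout to the microbiota. The Discussion expects high adherence, and patients receive a gift card for each completed time point. Because follow-up stool is collected at the hospital, early discharge of improved patients would bias the other way. This objection stands, and the point is therefore stated without a direction.

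**The wording is open.** The article does not say that each visit is tested separately, and it names PERMANOVA only as an example. Analysis sets and missing-data handling may sit in a fuller plan. That is fair, and no missing-data omission is alleged. What remains is the stated contrast, AN at each visit against HCs, which has the same limit in a single global model.

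**Within-patient change is planned elsewhere.** The mixed models address change within AN, which is how primary outcome ii is worded. Hypothesis 4 relates movement towards HCs to clinical improvement and so needs a per-patient measure. This narrows the point to the community-level statement of similarity to HCs. Hypothesis 4 concerns associations and does not test whether patients moved on average.

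**The size is modest.** At the article's own loss figure, the shift is about a third or less of the paired detectable change (0.10/0.28 = 36% at most). If loss depends on the observed TP1 value, it shrinks to about 0.6 × 0.05-0.10 = 0.03-0.06 SD. This stands too.

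**Conclusion.** The point holds in a limited, conditional form. As written, the only Hypothesis 2 analysis that measures similarity to HCs cannot separate change within patients from a change in who is sampled, and the bias could go either way.

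It would be too strong to say that loss will make the AN group look normalised. At about 10% loss the false shift is 0.05-0.10 TP1 SD, which would distort the gap but not remove it. It approaches a detectable change only at about 30% loss with leavers a full SD further away (0.30 against 0.32). The losses above 10%, the leaver difference, the test-retest and intraclass correlations and the simulation concentration are all assumptions.

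The alpha-diversity and taxon mixed models are not affected in this way, provided loss depends on values already observed.

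**What to change.** - Base the Hypothesis 2 normalisation statement on within-patient change. Compute each AN sample's beta-diversity distance to the HC group, for example to the HC centroid, and fit a mixed model of time with a patient random effect to all available visits.
- Keep the by-visit PERMANOVA against HCs as descriptive.
- As a sensitivity check, recompute the TP1 contrast in exactly the patients sampled at TP2 and at TP3.
- Report the TP1 distance to HCs of patients with and without later samples, so that readers can see whether loss was selective and in which direction.

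This changes analysis wording only; no sample or visit is added. The cost is a little more analysis, and the change test reduces beta diversity to a single distance score. The mixed model also relies on loss being explained by observed values, which the last item helps to judge but cannot prove. The wording should be settled before Hypothesis 2 is analysed.
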